## Discussion

The PRePP-projects aims to provide an elaborated understanding of factors predicting hospital readmission in palliative outpatients. As scarce knowledge is available on this issue and little comparable studies are available, we face some practical and operational challenges which future studies could keep in mind.

Representativity and generalizability could be limited as the project is a single-arm and single-center study. This may cause selection bias for certain patients’ and ICs’ characteristics regarding regional and cultural differences. A multicenter study design could reduce this kind of bias.

The different methods of collecting ICs’ data could induce varying response behavior. Participants acquired by mail or browser-based may feel more anonymous causing more reliable answers, compared to phone surveys. Possible bias due to social desirability while communicating directly with the study staff, could occur. Moreover phone surveys performed by different members of the study team could cause interviewer bias. However we decided to use the opportunity of phone surveys to keep response rate higher, considering elderly participants as not as comfortable using online questionnaires and avoid additional effort for them by returning the mail. As a practical issue we anticipate less participation of highly burdened ICs which could lead to an underestimation of participants' burden.

Concerning the questionnaires used, we face a trade-off between diagnostic accuracy on the one hand while reducing the burden for the participants on the other hand. We decided to administer short instruments such as GAD-7 or PHQ-9 as they use a smaller number of questions and are self-administered compared to structured interviews such as the Structured Clinical Interview for DSM-5 [37]. Furthermore, we aim to describe psychological burden rather than diagnose a psychiatric disease which allows for less sophisticated instruments. This is well in line with other groups performing research in palliative care [38].

As this study was conceptualized during the beginning of the COVID-pandemic there were no standardized questions reagarding ICs concerns about COVID available. Future research should progress on this issue, e.g. by developing standardized instruments or at least performing psychometric analyses on available questions.

Regardless of aforementioned challenges, the data obtained from the PRePP-Project serves as an important prerequisite for the development of a screening tool to predict readmission which could be administered to patients routinely in clinical practice.

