**Discussion:**

The PRePP-project is an important prerequisite for a clinical risk assessment of UHAs. Nevertheless, it faces several methodological challenges: as it is a single center study, representativity of results is limited while social desirability might be increased as the study is partly conducted by the treatment team. Furthermore, we anticipated an underrepresentation of highly burdened participants as they might refrain from participation.

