### Study measures

Informal caregivers willing to participate answer standardized measures on several domains.

Quality of Life will be assessed administering the WHOQOL-BREF [31], a 26-items inventory to assess a person’s Quality of Life including the four domains physical health, psychological, social relationships and environment. Higher scores denote higher Quality of Life in this domain.

Psychological distress will be assessed by the NCCN-Distress Thermometer [32] which comprises of a visual analogue scale ranging from zero to ten with higher scores indicating a more severe burden and a checklist of various symptoms. It is extensively used and cut-off data is available for use in an oncological setting [32]. Preliminary, it was developed for use in cancer patients while it might be applicable in other settings as well [33].

Anxiety will be assessed applying the Generalized Anxiety Disorder 7-item scale [34], a seven-items patient-reported questionnaire with sufficient psychometric properties. Scores range from zero to 21 on a single scale with higher scores indicating a higher level of anxiety. Results can be classified in either one of four classes ranging from minimal to severe anxiety symptoms.

Depressivness will be measured administering the Patient Health Questionnaire [35], which comprises of nine items. A single sum score is calculated which ranges from 0 to 27 with higher scores indicating a higher level of burden. Results are categorized in four classes ranging from no depressive symptoms to severe symptomatology.

Due to the possible influence of the current COVID-19 pandemic, four self-developed questions considering IC’s worries regarding an infection, changes in professional support and psychological burden due to preventive measures such as wearing a face mask were administered.

Nurses will answer two surprise questions [36], predicting whether they would be surprised when the patient will die within the next month (first question) and whether an UHA will occur during the next month (second question).

Characteristics of IC such as age, gender, and kind of relation to the patient, duration of daily care, highest education, and employment status will be obtained. Furthermore, the amount and type of professional support such as mobile nursing teams will be assessed.

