### Statistical analysis

The primary endpoint "number of unplanned inpatient admissions" is account variable. Univariate Poisson regressions will be used to analyze the association of structural factors and relative-reported factors or structural data with the primary endpoint. With the planned patient number of 240, it is possible to detect changes of 50% (corresponding to rate ratios of 1.5 and greater, given a base rate of 0.85) with a power of 95% if the influence variable is a binary categorical variable with 50% probability of occurrence. For a binary factor with a probability of occurrence of 90%, the detectable rate ratio with 95% power is still 2.0. For continuous, normally distributed influence variables, rate ratios of > 1.25 are detectable with 95% power.

Since a large number of factors are to be tested, the adjustment for multiple testing seems reasonable. According to the explorative approach of the study, the control of the false discovery rate is done by Benjamini–Hochberg procedure. *P* values of the univariate regression analyses that are < 0.05 after adjustment with the Benjamini–Hochberg procedure are considered significant. In the multivariable model, all parameters whose *p* values from the univariate analyses are < 0.1 after adjustment should be analyzed. The *p*-values of the multivariable model will not be adjusted.

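### Screening factors and refitting them on the same patients makes the rate ratios and p-values of selected factors optimistic, notably for weak-to-moderate effects, and the plan offers these results as groundwork for a screening tool

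*Protocol article*

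**What the plan says.** The Statistical analysis section of the protocol article fixes a sequence. Each factor is tested in a univariate Poisson regression on the number of unplanned hospital admissions (UHAs). The p-values are adjusted by Benjamini-Hochberg across what the article describes as many factors, without giving a count. The multivariable model then takes the parameters whose "values from the univariate analyses are < 0.1 after adjustment should be analyzed". The p-values of that model are not adjusted. The study is single-centre and no second dataset is described. The same section calls the approach explorative, and the primary aim under Study design and setting is to explore factors associated with UHAs.

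The intended use goes further. The Abstract calls the project "an important prerequisite for a clinical risk assessment of UHAs", and the last paragraph of the Discussion says the data "serves as an important prerequisite for the development of a screening tool to predict readmission", a tool that could be used routinely. The limitations listed in the Discussion do not mention that the final estimates come from data-driven selection.

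The sample size rests on "corresponding to rate ratios of 1.5 and greater, given a base rate of 0.85", with 240 patients.

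**The concern.** When the same data decide which factors are kept and how large their effects are, the kept estimates are pushed away from 1. A weak factor passes the screen mainly in samples where chance has enlarged it, and the refit uses that same sample. A factor with no effect that passes the screen tends to look significant again in the multivariable model, because its p-value there is not a fresh test.

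For a list of candidate associations this is tolerable if readers know it. It matters more when results are offered as groundwork for risk assessment. Whoever designs the later tool would look to the multivariable rate ratios and p-values to decide which factors to use and how heavily to weight them. Taken at face value, they would give predictions that are too extreme in new patients. Benjamini-Hochberg limits how many null factors enter; it does nothing about the size of the estimates that enter.

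**Working it through.** **Inputs from the Statistical analysis section.** N = 240; base rate 0.85; design rate ratios (RR) 1.5 (binary factor, 50% prevalence), 2.0 (90% prevalence) and above 1.25 (continuous factor, taken here as per SD); entry at adjusted p < 0.1.

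**Assumptions.** The number of candidates is not given: 30 in the main runs, 15 and 50 as a range. Five are real (not varied). Factors are independent with 50% prevalence, and there is no overdispersion unless stated.

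**The plan's own figure first.** For RR 1.5, var(log RR) = 1/(120 × 0.85) + 1/(120 × 0.85 × 1.5) = 1/102 + 1/153 = 0.01634, so SE = 0.1278 and z = ln(1.5)/0.1278 = 3.17. Power is Φ(3.17 − 1.645) = 93.7% one-sided and Φ(3.17 − 1.96) = 88.7% two-sided. The stated 95% is met to within 2 points only with a one-sided 5% test before multiplicity adjustment. This confirms how the inputs are used, with 0.85 as the rate when the factor is absent.

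**Why the screen inflates.** With an overall mean of 0.85 there are 240 × 0.85 = 204 expected events, and a balanced binary factor has SE ≈ √(4/204) = 0.140. With 30 candidates, a factor entering alone needs p < 0.1/30 = 0.0033, that is z > 2.94, an observed RR of at least exp(2.94 × 0.140) ≈ 1.51. If five enter, the last needs p < 0.1 × 5/30 = 0.0167, z > 2.39, RR ≥ exp(2.39 × 0.140) ≈ 1.40. A true RR of 1.25 can enter only when overestimated. A true RR of 2.0 clears the bar easily and is hardly selected on chance.

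**Simulation of the stated sequence** (univariate Poisson, Benjamini-Hochberg, entry at 0.1, refit; 30 candidates, 5 real). The result depends on how 0.85 is read:

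| 0.85 is the rate… | True RR | Mean RR of retained real factors | Calibration slope, new patients |
|---|---|---|---|
| averaged over all patients | 1.25 | about 1.55 | 0.37–0.39 |
| averaged over all patients | 1.5 | 1.61 | 0.74–0.76 |
| averaged over all patients | 2.0 | 1.99 | 0.93 |
| with one factor absent, others at their average | 1.2 | 1.52 | 0.33 |
| same | 1.3 | 1.50 | 0.59 |
| same | 1.5 | 1.54 | 0.83 |
| same | 2.0 | 1.97 | 0.96 |
| with all five real factors absent | 1.5 | 1.49 | 0.94–0.95 |
| same | 2.0 | 1.99 | 0.99 |

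The last reading implies an overall mean of 0.85 × 1.25⁵ ≈ 2.6 admissions at RR 1.5, so it is a favourable bound.

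Further results:
- **Number of candidates** (15, 30, 50; middle reading): RR 1.2 is read as 1.48–1.57, RR 1.3 as 1.47–1.54, RR 1.5 as 1.54–1.55. The same factors re-estimated in independent data come back at about 1.20, 1.30–1.31 and 1.50.
- **Null factors that were selected** (middle reading): unadjusted multivariable p < 0.05 in 92–97% of cases when the real factors have RR 1.2, 78–88% at 1.3, 53–68% at 1.5 and 15–18% at 2.0, against 3–6% in independent data.
- **Discrimination** (overall-mean reading, any UHA v none): c-statistic 0.62 apparent v 0.54 in new patients at RR 1.25; 0.68 v 0.63 at RR 1.5.
- **Continuous factors**, RR 1.25 per SD: read as about 1.27–1.28, slope 0.81–0.84.
- **Overdispersion** (variance parameter 0.5, middle reading): similar RR inflation, with slopes down to 0.40 at RR 1.3 and 0.66 at RR 1.5.
- **Empty models** (overall-mean reading): at RR 1.25 no factor is selected in 53–57% of studies. Slopes and c-statistics are for the remainder.

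**Does the remedy work?** Bootstrapping the whole sequence and shrinking by the resulting slope moved the new-patient slope from 0.38 to 0.55 at RR 1.25, from 0.60 to 0.80 at RR 1.35, and from 0.74 to 0.92 at RR 1.5 (overall-mean reading).

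**The case against.** The best defence is that the protocol promises little. It calls the analysis explorative, its aim is to explore associations, and it describes the data only as a prerequisite for a later tool. A reader might infer that this study's rate ratios will be carried into a tool as weights and that the tool will therefore be miscalibrated. The documents do not say so. That part of the defence stands.

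Second, the absence of shrinkage, calibration or discrimination measures is no error in itself, because a condensed article may leave these to a full protocol or analysis plan that is not shown. This also stands. The point rests on what the article does fix, namely the screen, the refit and the unadjusted p-values, set against the use it names.

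Third, inflation is not universal. It is small or absent at RR 1.5 if 0.85 is read as a rate without the risk factors, absent at RR 2.0, and modest for continuous factors at their design effect. With weak binary factors the model is often empty. All this is correct and sets the limits of the point. But nothing in the article suggests that every real factor reaches RR 1.5, and its Background describes the evidence as scarce.

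Fourth, one might ask that the model be compared with the nurses' forecast of "whether an UHA will occur during the next month". As a benchmark for a model of the total count this is mismatched, because the forecast covers one month. It is an optional extra only if matched to UHA occurrence in that month.

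The explorative label helps but does not settle the matter. It does not tell the reader how far the estimates are likely to shrink, and the Discussion still points them towards a tool.

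**Conclusion.** The point holds in a limited form. The stated sequence makes the rate ratios and unadjusted p-values of selected factors optimistic, and the article does not caution about this while offering the results as groundwork for risk assessment. Under the assumed 30 candidates with 5 real and an overall mean of 0.85, a true RR of 1.25 appears as about 1.55 and 1.5 as about 1.6, with slopes of about 0.4 and 0.75. At RR 2.0 there is no inflation. If 0.85 is the rate with all risk factors absent, inflation at RR 1.5 vanishes.

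These figures depend on the candidate count, independence and the reading of 0.85; overdispersion lowers the slopes. Nor should the refit be taken to use all 240 patients. Caregiver-reported factors exist only where a caregiver consents, and the article says that number cannot be predicted. A smaller analysis set would increase the optimism.

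It would be too strong to conclude that all reported rate ratios will be inflated. The problem lies with weak-to-moderate effects. It affects how results should be reported and reused, not whether the study can meet its exploratory aim.

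**What to change.** Keep the planned sequence and add the following:

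1. Bootstrap all of it in each resample: univariate tests, Benjamini-Hochberg, entry at adjusted p < 0.1, multivariable refit.
2. Report the optimism-corrected calibration slope and c-statistic from that bootstrap.
3. Print the multivariable log rate ratios multiplied by the corrected slope beside the raw ones, and name the shrunken values as those to inform any later tool.
4. Label the multivariable estimates and p-values as post-selection and exploratory, and add this to the limitations. State that bootstrap shrinkage only partly corrects weak effects (in the check above, a slope of 0.38 rose to 0.55, not to 1).

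The cost is some analysis code and one table, with no new data. The downside is that the reported rate ratios and discrimination will look less favourable.

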## Data Availability

The datasets used and/or analysed during the current study are available from the corresponding author upon reasonable request.

## Abbreviations

EAPC: European Association of Palliative Care
GAD-7: Generalized Anxiety Disorder 7-item scale
IC: Informal caregiver
NCCN: National Comprehensive Cancer Network
NP: Nursing practitioner
PHQ-9: Patient Health Questionnaire 9-item scale
SAPV: Specialized outpatient palliative care (German: Spezialisierte Ambulante Palliativversorgung, abbreviation: SAPV)
T0-T7: Time; indicates study visit
UHA: Unplanned hospital admission
